11.1 Formula’s

**1 General information**

- 1. **Organisation**

| Principle Investigator | - [name]: Neuro Critical Care, Azienda Ospedaliera Spedali Civili di Brescia, University of Brescia, (Italy) |
| --- | --- |
| Steering committee | - [name]: Neuro Critical Care, New York Presbyterian Hospital, Columbia University, New York (USA) - [name]: Neuro Critical Care, Addenbrooke’s NHS trust, Cambridge University, (UK) - [name]: Université Libre de Bruxelles , Hôpital Erasme, Brussels (Belgium) - [name]: Centre Hospitalier Universitaire Grenoble Alpes, Pôle Anesthésie Réanimation - [name]: Neuro Critical Care, Azienda Ospedaliera San Gerardo di Monza, Università degli studi Milano-Bicocca, (Italy) |
| **Coordinating center** | Neuro Critical Care Unit, Department of Anesthesiology, Intensive care, and emergency Medicine, Spedali Civili Hospital of Brescia, University of Brescia, Italy |
| Study Statistician | [name], Statistica medica e biometria, Statistician at the University of Brescia, Italy |
| **Data Management for IMPRESSIT-2 study purposes** | Study coordinators |

- 1. **Protocol summary**

| Title of the study | **Discriminant accuracy of Trans-Cranial Doppler to Exclude Intracranial Hypertension in Brain Injured Patients: The IMPRESSIT-2 Prospective Multicenter International Study** |
| --- | --- |
| **Primary outcome** | The NPV, PPV, sensitivity and specificity of ICPtcd estimation in excluding true intracranial hypertension, as measured by the gold standard invasive monitoring technique (ICPi). |
| **Design** | Prospective, observational, non-interventional, non-randomized, non-profit, international, multicenter, clinical study |
| Target population | **Inclusion criteria**   - Brain injury (Traumatic Brain Injury, Subarachnoid Hemorrhage, Intracerebral Hemorrhage, Ischemic stroke); - Patients requiring invasive ICP monitoring (Intraparenchymal, post-craniotomy or post-surgical, Intra-ventricular); - Age > 18 yrs.   **Exclusion criteria**   - inaccessible or poor acoustic ultrasound window, - a cardiovascular disease causing hemodynamic variations affecting the TCD reading (severe arrhythmia, severe cardiac valvular stenosis, moderate or severe vasospasm), - Patient already with craniotomy or craniectomy before first time frame 1°, - any treatment for suspected intracranial hypertension or manipulation of arterial blood pressure intervening between the non-invasive ICPtcd measurements and the insertion of invasive ICP (ICPi) measurement. |
| **Sample size** | 490 patients; (described in section 4.2) |
| **Interventions** | All patients included will have evaluation of non-invasive ICP monitoring through use of TCD (ICPtcd). ICPtcd will be calculated with the standard formula explained previously for non-invasive estimation of cerebral perfusion pressure (CPP)[Appendix11.1]*. (described in section 4.1). |
| **Study duration** | 24 months |

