# Finally, ICP is calculated:

# non-invasive ICP = MAP - non-invasive CPP [Appendix **]

# 3 Study endpoints

##

3.1 Primary outcome: the negative predictive value, positive predictive value, sensitivity and specificity of ICPtcd estimation in excluding true intracranial hypertension, as measured by the gold standard invasive monitoring technique (ICPi) [with catheters inserted either into the brain parenchyma or ventricles].

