**4 Study description**

##

4.1a Study design

*Non-invasive vs Invasive measurements.*

For each patient enrolled into the study, a total of three ICPtcd measurements will be performed in three different time frames, each of which will be compared to the corresponding ICPi for concordance.

- The first ICPtcd measurement (TIME 1) will be performed before ICPi placement (< 30 min.) and will be compared with the first ICPi reading once the probe is positioned. The need to reduce the time gap as much as possible between the two readings is motivated by the fact that ICP may be subjected to variations caused by ABP manipulation, cerebrospinal fluid (CSF) leakage during catheter placement and pharmacological treatment or fluctuations due to the evolving underlying brain injury.

-The second ICPtcd measurement (TIME 2) will be performed immediately after insertion of the ICPi probe and compared with the post-insertion ICPi reading. The ICPi measurement to be confronted with the ICPtcd estimated measurement for concordance must be read simultaneously.

- The third ICPtcd measurement (TIME 3) is performed between 2 and 3 hours following the second reading. The reason for this is to avoid any possible variations in systemic and cerebral hemodynamics caused by the ICPi device insertion itself, despite sedation. Therefore, performing the examination more than 2 hours post insertion should reduce the influence of the positioning maneuver on the readings. The ICPi measurement to be confronted with the ICPtcd estimated measurement for concordance must be read simultaneously.

In accordance with the present guidelines, intracranial hypertension is defined as an ICP above 22 mmHg, which remains so for at least 10 minutes and is not related to procedural pain [16]. Therefore, intracranial hypertension is considered such only when the ICPi reading meets this criteria.

However, when analysis will be performed the ICPtcd may be confronted to three different ICP values for concordance correlation (ICPi=20mmHg, ICPi=22mmHg, ICPi=25mmHg,).

*Patient sedation.*

Patient sedation for ICP bolt placement may consist of either bolus doses of sedatives and or analgesics and when necessary, neuromuscular blockade of choice, as long as these have been administered either before or after, and not between, the first concordance correlation. As mentioned previously this restriction is not necessary for the following two Time frames.

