# - any treatment for intracranial hypertension or manipulation of arterial blood pressure intervening between the non-invasive ICPtcd measurements and the invasive ICP (ICPi) measurement. (This is most likely to happen during time frame 1°). For this reason it is stressed that if the patient requires invasive ICPi monitoring to be performed in the operating room, than the non-invasive ICPtcd measurement should be performed just before the patient leaves the ICU (or if possible the ER) towards the OR for insertion. This would reduce the time during which the patient may be prone to ABP and ICP manipulation.

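### At TIME 1 the ICPtcd result comes before the reference and is not stated to be masked, while treatment in that interval excludes the patient, so exclusion can depend on the index test

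*Protocol*

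**What the plan says.** Section 4.1a puts the index test first at TIME 1: ICPtcd "will be performed before ICPi placement (< 30 min.) and will be compared with the first ICPi reading once the probe is positioned". At TIME 2 and TIME 3 the order does not matter, because "The ICPi measurement to be confronted with the ICPtcd estimated measurement for concordance must be read simultaneously".

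The ICPtcd value is available at the bedside as soon as the Doppler is done. Section 2 and Appendix 11.1 give it as simple arithmetic on arterial pressure and two flow velocities: "non-invasive ICP = MAP - non-invasive CPP".

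The exclusion criterion appears twice, in different words. The summary (section 1.2) excludes for "any treatment for suspected intracranial hypertension or manipulation of arterial blood pressure intervening between the non-invasive ICPtcd measurements and the insertion of invasive ICP". Section 5.2 excludes for "any treatment for intracranial hypertension or manipulation of arterial blood pressure intervening between the non-invasive ICPtcd measurements and the invasive ICP (ICPi) measurement". Section 5.2 adds that "This is most likely to happen during time frame 1". For probes placed in the operating room it says that "the non-invasive ICPtcd measurement should be performed just before the patient leaves the ICU", or the emergency room if possible.

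The visible text does not say whether the treating team sees the TIME 1 ICPtcd before the first ICPi is read. It also does not ask sites to record patients who are lost under this criterion.

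**The concern.** A diagnostic accuracy study needs entry into the analysis to be unrelated to the index result, or at least needs any relation to be visible. At TIME 1 three features combine: the index value is known first, it is not stated to be masked, and treatment given before the reference is read removes the patient.

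Before the probe is in, the Doppler figures are the only numerical estimates of ICP and CPP that the protocol provides for. Section 2 ties control of ICP to ICP and CPP values. A high ICPtcd could therefore contribute to the suspicion, or to the blood-pressure change, that triggers exclusion. Since ICPtcd is MAP minus estimated CPP, a high ICPtcd at a given MAP is the same thing as a low estimated CPP.

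Two of the four primary measures, sensitivity and specificity, would then be distorted in a known direction. The criterion is written per patient, so the excluded patient's TIME 2 and TIME 3 pairs would go too, and the time-averaged ROC analysis in section 9 would inherit the selection.

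**Working it through.** **The plan's own figure.** Section 4.2 assumes sensitivity 90%, prevalence 30%, power 95% and a lower limit of 10%, and gives N = 490. Read the 10% as ten points below 90%, that is 0.80, and assume a one-sided alpha of 0.05, which the section does not state. An exact binomial test of 0.90 against 0.80 then keeps power at or above 95% from 147 cases onward, and 147 / 0.30 = 490. The figure is reproduced.

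**Inputs for the bias.** Sensitivity Se = 0.90 and prevalence 0.30 are from section 4.2. Assumed, because the documents do not give them: specificity Sp, the fraction *a* of test-positives excluded, and the fraction *b* of test-negatives excluded. Given the test result, exclusion is taken to be unrelated to true status.

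**Formulas.**

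- Se' = Se(1 − a) / [Se(1 − a) + (1 − Se)(1 − b)]
- Sp' = Sp(1 − b) / [Sp(1 − b) + (1 − Sp)(1 − a)]

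**Main case, Sp = 0.70 and b = 0.05.**

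- a = 0.05: equal loss in both groups, so no bias (90.0% and 70.0%).
- a = 0.20: Se' = 0.720 / (0.720 + 0.095) = 0.883; Sp' = 0.665 / (0.665 + 0.240) = 0.735.
- a = 0.40: Se' = 0.540 / (0.540 + 0.095) = 0.850; Sp' = 0.665 / (0.665 + 0.180) = 0.787.

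**Range, with no test-negatives excluded (b = 0).**

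| a | Se' | Sp' if Sp = 0.70 | Sp' if Sp = 0.80 | Sp' if Sp = 0.90 |
| --- | --- | --- | --- | --- |
| 10% | 0.890 | 0.722 | 0.816 | 0.909 |
| 20% | 0.878 | 0.745 | 0.833 | 0.918 |
| 30% | 0.863 | 0.769 | 0.851 | 0.928 |
| 50% | 0.818 | 0.824 | 0.889 | 0.947 |

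**How much exclusion brings sensitivity to 0.80.** With b = 0.05, 0.9(1 − a) must equal 4 × 0.095 = 0.38, so a = 58%. With b = 0, it must equal 4 × 0.10 = 0.40, so a = 56%.

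**Predictive values.** Per patient, at Sp = 0.70, true positives are 0.30 × 0.90 = 0.27 and false positives 0.70 × 0.30 = 0.21, so PPV = 0.27 / 0.48 = 0.562. False negatives are 0.03 and true negatives 0.49, so NPV = 0.49 / 0.52 = 0.942. Exclusion multiplies both terms of PPV by (1 − a) and both terms of NPV by (1 − b). The factors cancel and neither value moves.

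**Cases.** If the exclusions come out of the 490, a = 0.20 and b = 0.05 leave 147 × (0.720 + 0.095) = about 120 cases. Recruiting replacements would restore the total but not undo the selection.

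**The two wordings.** Section 1.2 has *suspected* and ends the interval at insertion of the probe. Section 5.2 omits *suspected* and ends the interval at the ICPi measurement. A patient treated after insertion but before the first reading is excluded under one wording and not under the other.

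**The case against.** The strongest reply is that the causal link is not documented. The study is described as non-interventional, patients are to receive guideline care, and section 4.1a counts hypertension as present only when ICPi meets the definition. Every enrolled patient already requires invasive monitoring, so suspicion may rest on CT or clinical signs that predate the Doppler, and blood pressure may be changed for unrelated reasons. This stands: a reader might infer that ICPtcd steers treatment in this study, and the documents do not support that. They leave the route open and say nothing more. Calling the estimator unvalidated would also go too far, since section 2 reports earlier accuracy for it.

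The exclusion has a sound purpose, because treatment between the two readings would break the comparison. The plan also shortens the exposure: less than 30 minutes, measurement just before departure for the operating room, and no sedative or analgesic between the TIME 1 readings. That also stands, but a shorter interval reduces dependence on the result without removing it or making it visible.

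A third reply is that this is an omission, and that the flow diagram in section 6, which is not visible, or the data form could deal with it. That is possible. Still, masking and eligibility are protocol matters, and the written rule as it stands lets the index result affect who is analysed.

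Finally, a reader might infer that all four primary measures are biased. They are not, if exclusion depends only on whether ICPtcd is positive. NPV, the measure closest to the title's aim of excluding hypertension, is then unchanged. If sicker patients are also treated more often at the same ICPtcd, PPV and NPV move as well. The word *suspected* on its own matters little, because before the probe is in, hypertension as section 4.1a defines it cannot be established.

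**Conclusion.** The point holds as a design weakness with a known direction and an unknown size. The written rules allow exclusion at TIME 1 to depend on the ICPtcd result. If it does, observed sensitivity is too low and specificity too high, while PPV and NPV are spared under dependence on ICPtcd alone.

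Under the assumptions shown (sensitivity 90%, specificity 70%, 5% of test-negatives lost), the shift at 20% loss of test-positives is 1.7 points down in sensitivity and 3.5 points up in specificity. At 40% loss it is 5.0 down and 8.7 up. Only a loss of well over half of test-positives would bring sensitivity to 80%. The exclusion fractions and the specificity are assumptions, and the documents cannot narrow them. The remedy is a worthwhile, cheap improvement; nothing here shows that the planned results would be invalid.

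**What to change.** 1. In section 4.1a, have sites enter FVd, FVm and MABP at TIME 1. REDCap computes ICPtcd and displays it only after the first ICPi value is saved. This withholds a research calculation; it leaves usual-care Doppler reporting unchanged and sets no rule on treatment.
2. Log every patient excluded under this criterion with the TIME 1 inputs and the first ICPi. Report the number excluded by ICPtcd result, so that selective loss can be measured even where masking fails.
3. Add a sensitivity analysis that includes these patients. Read it as a check on the main result and not as a replacement, because their first ICPi follows the treatment or blood-pressure change.
4. Reconcile sections 1.2 and 5.2 on *suspected* and on whether the interval ends at insertion or at measurement.

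The cost is a calculated, locked field, a few extra form fields and a few sentences of protocol text. The downside is that concealment is partial: the operator sees the velocities and can work out the formula by hand. That is why the log matters as much as the masking.

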**2 Rationale and aim of the study**

As part of intensive treatment of brain injury, intracranial pressure (ICP) should be controlled when the cerebral perfusion pressure (CPP) falls below 70mmHg (depending on the cause of injury) and/or the ICP is greater than 22mmHg for > 10 min. Intracranial hypertension (ICHP) occurs in approximately 40% of all patients with severe traumatic brain injury and is not infrequent in patients with non traumatic brain injury, such as subarachnoid hemorrhage (SAH), spontaneous intracerebral hemorrhage (ICH), and ischemic stroke (IS), and the presence of ICHP and inadequate CPP has been correlated to bad outcome. Therefore, measures to monitor ICP and CPP should be instituted as soon as possible in patients with severe brain injury.

*Monitoring.* Monitoring of patients with brain injury (BI) is essential for the guidance and optimization of therapy. The rationale of monitoring is early detection and diagnosis of secondary brain insults, both systemic and intracranial and must comprise both general and specific neurologic monitoring. The Brain Trauma Foundation (BTF) guidelines for TBI management recommends that ICP should be monitored in all salvageable patients with severe TBI and an abnormal computed tomography (CT) scan. Based on physiological principles, potential benefits of ICP monitoring include earlier detection of intracranial mass lesion, guidance of therapy and avoidance of indiscriminate use of therapies to control ICP, drainage of cerebrospinal fluid (CSF) with reduction of ICP and improvement of CPP, and determination of prognosis. Currently, available methods for ICP monitoring include epidural, subdural, subarachnoid, parenchymal, and ventricular locations. Historically, ventricular ICP catheter has been used as the reference standard and the preferred technique when possible. It is the most accurate, and reliable method of monitoring ICP [1]. Subarachnoid, subdural, and epidural monitors are less accurate. Unfortunately, all of the described methods are invasive, associated with a complication rate and are not inexpensive.

*Transcranial Doppler*. New methods have been developed in order to measure ICP non-invasively. Transcranial Doppler (TCD) for example, is a technique for monitoring cerebral hemodynamics, introduced by Aaslid et al in 1982. [4]. By using a low-frequency–pulsed Doppler of 2MHz over the acoustic window regions—where the skull bone is thin—or at the foramen magnum, it is possible to measure flow velocities in the basal cerebral arteries. A broad spectrum of usage scenarios for TCD have been proposed, including detection of vasospasm in SAH, detection of cerebral embolization, and arterial steno-occlusive disease, evaluation of collateral circulation, evaluation of recanalization, cerebrovascular autoregulation, detection of cerebral circulatory arrest, and for measuring ICP. [5,6]. The American Society of Neuroimaging’s Practice Guidelines Committee has developed standardized guidelines for TCD performance.[7,8]. TCD Technique and ICP In 1987, Klingelhofer and colleagues first described a relationship between increasing ICP and decreasing TCD-derived flow velocities and an increase in the Pourcelot index or resistance index (RI), defined as RI= (FVpeak sys_FVend dia)/(FVpeak sys). [9,10,11].

Aaslid *et al.* suggested that an index of CPP could be derived from the ratio of the amplitudes of the first harmonics of the ABP and the MCA velocity (detected by transcranial Doppler sonography) multiplied by mean flow velocity. Recently, a method for the non-invasive assessment of CPP has been reported, derived from mean arterial pressure multiplied by the ratio of diastolic to mean flow velocity. This estimator can predict real CPP with an error of less than 10 mm Hg for more than 80% of measurements. This is of potential benefit for the continuous monitoring of changes in real CPP over time in situations where the direct measurement of CPP is not readily available. [12].

# *Non-invasive CPP measurement.* A more complex method aimed at the non-invasive assessment of ICP has been introduced and tested by Schmidt *et al.* The method is based on the presumed linear transformation between arterial pressure and ICP waveforms. Coefficients of this transformation are derived from the database of real ABP and ICP recordings. Similar linear transformation is built, using the same database between flow velocity and arterial pressure. Then the model assumes linear relationship between arterial pressure and flow velocity and arterial pressure to ICP transformations. Multiple regression coefficients are calculated. [13-15].

#

# estimated-CPP: MAP x diastolicFV-mca / meanFVmca + 14

*Non-invasive ICP measurement.*

# Finally, ICP is calculated:

# non-invasive ICP = MAP - non-invasive CPP [Appendix **]

# 3 Study endpoints

##

3.1 Primary outcome: the negative predictive value, positive predictive value, sensitivity and specificity of ICPtcd estimation in excluding true intracranial hypertension, as measured by the gold standard invasive monitoring technique (ICPi) [with catheters inserted either into the brain parenchyma or ventricles].

**4 Study description**

##

4.1a Study design

*Non-invasive vs Invasive measurements.*

For each patient enrolled into the study, a total of three ICPtcd measurements will be performed in three different time frames, each of which will be compared to the corresponding ICPi for concordance.

- The first ICPtcd measurement (TIME 1) will be performed before ICPi placement (< 30 min.) and will be compared with the first ICPi reading once the probe is positioned. The need to reduce the time gap as much as possible between the two readings is motivated by the fact that ICP may be subjected to variations caused by ABP manipulation, cerebrospinal fluid (CSF) leakage during catheter placement and pharmacological treatment or fluctuations due to the evolving underlying brain injury.

-The second ICPtcd measurement (TIME 2) will be performed immediately after insertion of the ICPi probe and compared with the post-insertion ICPi reading. The ICPi measurement to be confronted with the ICPtcd estimated measurement for concordance must be read simultaneously.

- The third ICPtcd measurement (TIME 3) is performed between 2 and 3 hours following the second reading. The reason for this is to avoid any possible variations in systemic and cerebral hemodynamics caused by the ICPi device insertion itself, despite sedation. Therefore, performing the examination more than 2 hours post insertion should reduce the influence of the positioning maneuver on the readings. The ICPi measurement to be confronted with the ICPtcd estimated measurement for concordance must be read simultaneously.

In accordance with the present guidelines, intracranial hypertension is defined as an ICP above 22 mmHg, which remains so for at least 10 minutes and is not related to procedural pain [16]. Therefore, intracranial hypertension is considered such only when the ICPi reading meets this criteria.

However, when analysis will be performed the ICPtcd may be confronted to three different ICP values for concordance correlation (ICPi=20mmHg, ICPi=22mmHg, ICPi=25mmHg,).

*Patient sedation.*

Patient sedation for ICP bolt placement may consist of either bolus doses of sedatives and or analgesics and when necessary, neuromuscular blockade of choice, as long as these have been administered either before or after, and not between, the first concordance correlation. As mentioned previously this restriction is not necessary for the following two Time frames.

Mechanical ventilation should be targeted to maintain adequate oxygenation (SaO2 > 90%) and normocapnia (PaCO2 36–40 mmHg). Intravenous fluids and inotropic support (norepinephrine and/or epinephrine) are appropriate in order to achieve and maintain a sufficient cerebral perfusion pressure (CPP >60 mmHg). General management of the various types of brain injury (traumatic, hemorrhagic, or ischemic), as well as the definition of intracranial hypertension, should be in accordance to international guidelines [16]. Treatment of intracranial hypertension was based on a protocol-driven strategy which included optimization of arterial blood pressure and volemia, sedation, mild hyperventilation, and infusion of hyperosmolar fluids [17].

*Patient monitoring.*

Systemic hemodynamic monitoring will consists of invasive arterial blood pressure (ABP) from the radial artery, continuous electrocardiography and pulse oximetry. ICPi may be performed either by means of an intraparenchymal fiberoptic transducer or a catheter inserted into the brain ventricles and connected to an external pressure transducer and drainage systems (external ventricular drain).

For CPP calculation. the arterial transducer should be leveled at the height of the external auditory meatus of the ear, or tragus.

Cerebral blood flow velocity will be assessed using TCD sonography and should be performed by a selected group of experienced operators in order to reduce inter-operator variability.

The insonation technique is standard: a low frequency pulsed 2 MHz ultrasound probe to be placed over the acoustic temporal window for insonation of the M1/M2 section of the middle cerebral artery (MCA) at a depth ranging from 45 to 55 mm. The MCAs are to be insonated bilaterally; however, for ICPtcd measurements, the acoustic window ipsilateral to the side of ICP bolt placement is preferred. The Doppler parameters necessary for calculation on ICPtcd are:

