**9 Statistical analysis**

Receiver operating curve (ROC) and the area under the curve (AUC) will be estimated after measurement averaging over time and as well as using time-dependent ROC. Values of ICPi will be dichotomized using a standard reference value of 22 mmHg. Confidence interval for AUC, sensitivity and specificity will be computed using bootstrapping (B = 10000). The sensitivity is expressed as the probability that a patient with high ICPi (>22 mmHg) would also have a high ICPtcd value, and the specificity as the probability that a patient with normal ICPi (≤22 mmHg) would also have a normal ICPtcd value. Best threshold for marker will be computed using Youden criterion [18–21].

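### At TIME 2 and TIME 3 nothing keeps the TCD operator from knowing the ICPi value, and the side used for ICPtcd is preferred but not fixed, so accuracy at these frames may be overstated

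*Protocol*

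**What the plan says.** Protocol section 4.1a defines three paired measurements per patient.

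- **TIME 1:** the TCD "will be performed before ICPi placement (< 30 min.) and will be compared with the first ICPi reading once the probe is positioned".
- **TIME 2:** the TCD "will be performed immediately after insertion of the ICPi probe and compared with the post-insertion ICPi reading".
- **TIME 3:** the TCD "is performed between 2 and 3 hours following the second reading".

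For TIME 2 and TIME 3 the section adds: "The ICPi measurement to be confronted with the ICPtcd estimated measurement for concordance must be read simultaneously".

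The patient monitoring paragraph of the same section sets the insonation depth at 45 to 55 mm and the side as follows: "The MCAs are to be insonated bilaterally; however, for ICPtcd measurements, the acoustic window ipsilateral to the side of ICP bolt placement is preferred". On operators it says that the TCD "should be performed by a selected group of experienced operators in order to reduce inter-operator variability".

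Section 3.1 makes NPV, PPV, sensitivity and specificity the primary outcome. Section 9 says that the ROC curve and AUC "will be estimated after measurement averaging over time and as well as using time-dependent ROC", with ICPi dichotomised at 22 mmHg.

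The protocol does not say who reads ICPi, whether the TCD operator may see it, or in what order the two values are recorded.

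**The concern.** TCD depends on the operator. Someone chooses the side and the tracing that supply FVd and FVm. An operator who knows the ICPi value while making that choice can, without intending to, settle on the reading that agrees better. The error of the index test then shrinks for a reason that would not exist in practice, where TCD is meant to be used without an invasive probe. All the primary accuracy measures move upward together.

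Two of the three pairs per patient are open to this, and section 9 uses all three frames. The formula itself is objective, but its inputs are not fixed in advance. A reading taken with knowledge of ICPi cannot be corrected in the analysis, so this belongs in the conduct section of the protocol and not in a later analysis plan.

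**Working it through.** **What the text allows.** At TIME 1 no ICPi exists when the TCD is done, so the TCD is masked by design. At TIME 2 and TIME 3 the probe is in place and the readings are simultaneous, with no masking, no separate reader and no recording order. The one safeguard on operators, their experience, is there to reduce inter-operator variability. Both sides are measured, and the ipsilateral default has no criterion for departure.

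**How sensitive ICPtcd is to the tracing.** From the appendix (11), ICPtcd = MAP − (MAP × FVd/FVm + 14) = MAP × (1 − FVd/FVm) − 14. At an assumed MAP of 90 mmHg, a change of 0.05 in FVd/FVm moves ICPtcd by 90 × 0.05 = 4.5 mmHg. Near 22 mmHg that can reclassify a reading.

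**Inputs for the size.** The 30% prevalence is from section 4.2 and the 22 mmHg threshold from section 9. Section 2 states a CPP error below 10 mmHg in more than 80% of measurements. With normal, unbiased errors this implies an SD of up to 10/1.2816 = 7.8 mmHg, and ICPtcd carries the same error because it is MAP minus estimated CPP. The ICP SD of 8 mmHg, the correlation ρ between the errors of the two sides (0 to 0.9) and the share of readings in which the closer side is kept are assumptions.

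**Effect on the error SD.** If the side closer to ICPi is kept in a share s of readings, the error variance is multiplied by 1 − s × (2/π) × √(1 − ρ²).

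- s = 1, ρ = 0: 1 − 0.637 = 0.363, so SD = 7.8 × √0.363 = 4.7.
- s = 1, ρ = 0.9: 1 − 0.637 × 0.436 = 0.722, so SD = 7.8 × √0.722 = 6.6.
- s = 0.25, ρ = 0: 1 − 0.159 = 0.841, so SD = 7.8 × √0.841 = 7.15.
- s = 0.25, ρ = 0.9: 1 − 0.069 = 0.931, so SD = 7.8 × √0.931 = 7.5.

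**Effect on accuracy, single reading (simulation, ICPtcd cut-off 22 mmHg).**

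| Closer side kept | AUC | NPV |
|---|---|---|
| Never (side fixed) | about 0.845 | 0.868 |
| In 25% of readings, ρ 0.9 to 0 | 0.853 to 0.863 | up by about 0.6 to 1.1 points |
| Always, ρ 0.9 to 0 | 0.88 to 0.92 | 0.89 to 0.91 |

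Other assumed inputs (error SD 5, 8 or 10 mmHg, ρ 0.5 or 0.8) gave the same direction throughout. With 25% selection, sensitivity rose by 1.2 to 2.0 points and NPV by 0.6 to 1.1 points.

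**Effect on the three-frame average.** If true ICP is the same at all three frames, frame errors are independent, TIME 1 is unaffected, and 25% of TIME 2 and TIME 3 readings are selected, the AUC of the averaged value rises by about 0.003 to 0.006.

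**Sample size.** Section 4.2 states 490. An exact binomial calculation for sensitivity 0.90 against 0.80 (reading the 10% as ten points), with an assumed one-sided alpha of 0.05 and power 95%, gives 147 cases as the number from which power stays at or above 95%. Then 147/0.30 = 490. Masking and side do not enter, so N does not change.

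**The case against.** The strongest case on the other side has four parts.

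- **The side is not a free choice.** The protocol says that "for ICPtcd measurements, the acoustic window ipsilateral to the side of ICP bolt placement is preferred", which is a default tied to the reference device. This stands. A reader might infer that the operator may use either side at will, and the text does not support that. What remains is that the default is not binding and departures have no rule.
- **Visibility is inferred.** The protocol never says that the TCD operator sees ICPi. Simultaneous reading is also sound, because ICP fluctuates and the pair must match in time. This stands too. The defect is the missing safeguard beside that requirement, not the requirement itself.
- **The larger figures are a ceiling.** An AUC of 0.88 to 0.92 needs the closer side to be reported every time, against the stated default. The 0.92 end also needs unrelated errors on the two sides, which is unlikely when both share one MAP and one constant. These figures should not be read as expected effects. Depth matters less than it may seem, since a scale factor common to FVd and FVm cancels in the ratio. Selection of depth or tracing has not been quantified.
- **The frames differ in other ways.** TIME 1 has the pre-insertion gap, and section 4.1a itself names CSF leakage and the insertion manoeuvre. A difference between TIME 1 and the later frames could not be put down to masking alone, and the protocol states no hypothesis comparing frames.

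None of this supplies the missing masking or a binding side rule.

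**Conclusion.** The point holds as a risk of upward bias in the primary accuracy measures at TIME 2 and TIME 3. A reader might go further and conclude that accuracy is overstated. The documents do not show that, since nothing in them indicates that any reading would be selected.

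The direction is upward in every scenario tried, but the size is unknown. It is modest if selection is occasional and smaller still in the three-frame average. All these figures rest on assumed error SD, ICP SD, side correlation and selection share, and they cover choice of side only. It is worth correcting because the primary outcome is accuracy itself, the remedy is cheap, and later analysis cannot repair readings already taken.

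**What to change.** In section 4.1 state that:

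- the ipsilateral side is primary, the contralateral side is used only if no ipsilateral signal is obtained, and both sides are recorded;
- the TCD operator records and locks FVd, FVm, MAP, side and time before viewing or entering the paired ICPi, with the ICP display turned away or covered from the operator's view where care allows;
- ICPi for that time stamp comes from the stored monitor record where available, and otherwise from bedside staff already present;
- ICPtcd is calculated centrally with the formula in 11.1;
- TIME 1 accuracy is also reported separately, as the naturally masked check on the TCD side.

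**Cost.** This needs a field order and lock in the RedCap form already planned (section 7.1), and slightly more procedure at the bedside. The lock alone does not mask an operator who has a live monitor in view, so masking will be incomplete at some bedsides. The documents do not establish that every site stores ICPi trends, so some sites will depend on the bedside reading. N stays 490.
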